### Data collection

#### Patient characteristics

Patient characteristics that include age, gender, household income, ethnicity, and education will be collected at baseline. Also, a measure of comorbidity [58], medication risk [59], frailty [60], and beliefs about medicines [61] will be completed. Patient preferences, priorities, and goals are recorded as part of the clinical intervention.

### Outcome measures

Primary and secondary outcomes will be measured at *T*_0_ and *T*_6_ for effectiveness analyses (Research Questions 1 and 2, Fig. 2). See Additional File 4 for a detailed description of the outcome measures and how they relate to the data analysis plan respectively, and Additional File 5 for the detailed schedule of all data collection. Choice of measures was guided by recommendations from an international consensus that identified a set of outcomes specific for multimorbidity patients [62], evidence of their relationship to polypharmacy [8, 9, 12], and piloting of a number of measures in our feasibility RCT (reported elsewhere) [42].

**Fig. 2 Fig2:**
[figure not shown]
SPIRIT figure with study timeline and data collection time points

#### Primary outcome measure

The primary outcome includes the number of prescribed medications per patient at baseline and 6 months (see Additional File 4 for definition). Locally acting topical agents without substantial systemic absorption or effects are not included. Acute short-course medications such as antibiotic prescriptions are not included in the counts. This will be ascertained by a pharmacist by performing a medication reconciliation using dispensing information, the electronic medical record, and patient information. Discrepancies will be resolved by discussing with the patient and dispensing pharmacist.

#### Secondary outcome measures

Unless specified, all outcome measures are recorded at baseline and 6 months (see Additional File 4). Constructs included as secondary outcomes include disease burden, treatment burden, quality of life, cognition, fatigue, nutritional status, physical function capacity and ability, falls, pain, sleep, patient enablement, medication self-efficacy, and healthcare utilization.

Other medication-related information will be recorded to identify and describe the processes of medication change during the intervention. Simple descriptive data will be reported on the following process measures:
Number of medications with persistent discontinuation at 6 monthsNumber of medications re-initiatedNumber of medications switched to safer medication,Number of medications with dose change (decrease), and dose change (increase)Number of medications initiatedNumber of recommended medication changesNumber and description of medication changes aligned with patient priorities and goals

TaperMD includes a prompt for “completed status” for every medication that includes all these options. Data will be collected through an audit of TaperMD records and progress notes, EMR, and dispensing records. We will describe any observed patterns in groupings of discontinued medications, in particular among those associated with adverse drug reactions causing hospital admissions.

### Adverse events, harms, and beneficial withdrawal effects

Adverse events potentially related to medication withdrawal, potential medication side effects unmasked by discontinuation (i.e., symptom relief), new or worsening side effects, and emergency department visits will be collected by solicited inquiry as well as spontaneous patient or clinician report. The definition from the Common Terminology Criteria for Adverse Events (CTCAE) of Severe/Serious Adverse Event will be used in this study: Any event that requires in-patient hospitalization or prolongation of existing hospitalization, causes congenital malformation, results in persistent or significant disability or incapacity, is life-threatening, or results in death [63]. All adverse events and harms will be summarized and reported with the trial results.

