#### STEP 2: Pharmacist consultation

The patient will meet first with the pharmacist to review the list of medications for reconciliation with what the patient reports they are taking, including accuracy of dose and frequency and indications. Specific side effect inquiry is recorded for each medication as well as any further relevant patient characteristics. A medication review will be done, focused on medications suitable for stopping or dose reduction, supported by the TaperMD screen and evidence resources for tapering, the reported medication side effects from the patient, and review of the patient’s medication experience and priorities and preferences for treatment.

The pharmacist will make initial recommendations focused on medications suitable for discontinuation or dose reduction and record these in TaperMD, which will then be visible to the family physician. The summary of this initial plan will also be integrated into the pharmacist’s electronic record.

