### Monitoring

Study participants will be followed for 6 months. Participants will attend monitoring visits, as clinically indicated, with the most appropriate clinician during the “pause and monitor” phase and informed by the tools supporting tapering and monitoring. Planned monitoring visits will be recorded in TaperMD and pulled into the EMR as the visit record. Participants will have no restrictions on other clinical activities.

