### Control group

The control group will receive usual clinical care. The only restriction is there will be no other planned medication reviews performed in the primary care setting during this phase. Patients carry information requesting no routine medication deprescribing settings for the 6-month period, except if medically indicated. Control patients will be offered the intervention after their 6-month outcome assessment. This comparator was chosen as it was felt this approach was likely to reduce contamination bias and maximize recruitment.

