### Check-in data collection

To facilitate accurate recall of adverse events, healthcare utilization, and changes in symptoms or side effects throughout the study duration, telephone check-ins will occur at 1 week, 3 months, and 6 months post-baseline to enquire specifically about these items. Details of any adverse effects identified at these data collection points will be provided in real time to the family physician and pharmacist to address as clinically appropriate. The research ethics board will be notified of any adverse events felt to be study related.

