What is the effect of a structured medication discontinuation clinical pathway designed to reduce polypharmacy on patient quality of life, cognition, mobility-related fatigue, nutritional status, physical function capacity, pain, sleep, patient enablement, medication self-efficacy, medication confusion, grip strength, falls and adverse events, and hospital admissions compared to usual practice?	Improved disease and treatment burden, quality of life, cognition, fatigue, nutritional status, physical function capacity and ability, pain, sleep, patient enablement, medication self-efficacy and lower/fewer falls, healthcare utilization, and adverse events will be reported in the intervention arm compared to the control arm at 6-months	Disease burden	*T*_0_, *T*_6_	Linear regression
		Treatment burden	*T*_0_, *T*_6_	Linear regression
		Quality of life	*T*_0_, *T*_6_	Linear regression for all continuous outcomes, Logistic regression for Categorical outcomes and Count data models (e.g., Poisson/negative binomial regression, zero-inflated models) for count outcomes
			*T*_0_, *T*_6_	
		Cognition	*T*_0_, *T*_6_	
		Fatigue	*T*_0_, *T*_6_	
		Nutritional status	*T*_0_, *T*_6_	
		Physical function capacity and ability	*T*_0_, *T*_6_	
			*T*_0_, *T*_6_	
			*T*_0_, *T*_6_	
			*T*_0_, *T*_6_	
		Number of Falls	*T*_0_, *T*_6_	
		Pain	*T*_0_, *T*_6_	
		Sleep	*T*_0_, *T*_6_	
		Patient enablement	*T*_0_, *T*_6_	
		Medication self-efficacy	*T*_0_, *T*_6_	
		Healthcare resource utilization (number of hospitalizations, emergency department visits, primary care visits, proportion of patients with at least one hospitalizations)	*T*_0_, *T*_6_	
			*T*_0_, *T*_6_	
			*T*_0_, *T*_6_	
			*T*_0_, *T*_6_	
		Number of Serious adverse events and beneficial withdrawal	*T*_1_, *T*_3_, *T*_6_	
What is the cost-effectiveness of the structured medication discontinuation clinical pathway designed to reduce polypharmacy?	Not applicable	Cost per QALY	*T*_6_	Cost utility analysis
What is the experience of patients as they go through a structured medication discontinuation clinical pathway designed to reduce polypharmacy?	Not applicable	Lived experience with deprescribing process	*T*_6_	Descriptive analysis of Semi-structured interview/patient diaries
		Satisfaction with the intervention (5-point Likert scale)	*T*_6_	Descriptive statistics (M, SD)
		Satisfaction with care around medications (5-point Likert scale)	*T*_0_, *T*_6_	Linear regression

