### Contamination

Access to TaperMD is by individual record unique ID. Pharmacists and physicians will only be able to access TaperMD intervention patients. Access will only be available for control patients after they have passed through the 6-month data collection point.

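### Harms reports from unequal clinician contact are combined with calls common to both arms, leaving the comparison of non-serious events, side effects and beneficial withdrawal effects open to detection bias

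*Protocol article*

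**What the plan says.** **Sources.** The protocol article's section on adverse events, harms and beneficial withdrawal effects covers four kinds of event: those possibly due to withdrawal, side effects that lift on stopping a drug, new or worsening side effects, and emergency department visits. They "will be collected by solicited inquiry as well as spontaneous patient or clinician report". The section adds that "All adverse events and harms will be summarized and reported with the trial results" and mentions no separation by source.

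**Contacts that appear common to both arms.** Under Check-in data collection, "telephone check-ins will occur at 1 week, 3 months, and 6 months post-baseline to enquire specifically about these items". No arm is excluded.

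**Contacts in the TAPER arm only, before month 6.** At the pharmacist consultation (Step 2), "Specific side effect inquiry is recorded for each medication". A family physician consultation follows (Step 3). Under Monitoring, "Participants will attend monitoring visits, as clinically indicated, with the most appropriate clinician" during the pause-and-monitor phase.

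**Control arm.** "The control group will receive usual clinical care", with no planned medication review. For the TaperMD platform, the Contamination section says: "Access will only be available for control patients after they have passed through the 6-month data collection point".

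**Use of the data.** The Table 1 hypothesis is that "lower/fewer falls, healthcare utilization, and adverse events will be reported in the intervention arm compared to the control arm". The only harms row in that table counts serious adverse events and beneficial withdrawal at T1, T3 and T6. The Sample size section also claims that 160 per group can detect drug-related side effects of 10% versus 25%.

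**The concern.** A count of reported events is the product of how often events occur and how often they are noticed and recorded. Randomisation balances the first. It does not balance the second if one arm sees clinicians more often, for the express purpose of looking for drug effects, and those clinicians' reports enter the same count.

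With the same true rate in both arms, the combined count would then tend to show more events under TAPER. With a true benefit, the observed benefit would shrink. Beneficial withdrawal effects are affected too: more of them would be recorded in the arm that is watched more closely, and there the tilt favours TAPER. Blinding the outcome assessor does not help, because the imbalance lies in reports that reach the study through patients and treating clinicians. The article also rules out a data monitoring committee, so the final between-arm summary is an important part of the safety evidence.

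**Working it through.** **1. The plan's own figure.** Inputs from Sample size and Quantitative data analysis: 10% versus 25%, two-sided 5%, 80% power, 160 per group.

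n = [1.96·√(2·0.175·0.825) + 0.8416·√(0.10·0.90 + 0.25·0.75)]² / 0.15² = (1.053 + 0.443)² / 0.0225, which rounds up to 100 per group.

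Power at 160 per group is 94.5%. The article's statement that 160 suffices is correct, provided detection is complete and equal in both arms.

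**2. Contacts before month 6, side by side.**

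| Channel | TAPER | Control |
|---|---|---|
| Scheduled calls (1 week, 3 and 6 months) | yes | yes (no arm restriction stated) |
| Pharmacist side-effect inquiry per drug | yes, before tapering | no |
| Study physician review | yes | no |
| Pause-and-monitor visits | yes, frequency not given | no |
| Usual care, spontaneous report | yes | yes |

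The channels differ in clinician contact and not in the calls.

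**3. Detection model (all rates assumed).** Let s be the share of events found by the calls. Let v and c be the shares of the remainder found by other channels in TAPER and in control.

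Detection in TAPER = s + (1 − s)v. Detection in control = s + (1 − s)c.

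With equal true rates, the observed ratio is the first divided by the second:

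| s | v | c | TAPER | Control | Ratio |
|---|---|---|---|---|---|
| 0.6 | 0.50 | 0 | 0.80 | 0.60 | 1.33 |
| 0.6 | 0.25 | 0 | 0.70 | 0.60 | 1.17 |
| 0.8 | 0.50 | 0 | 0.90 | 0.80 | 1.13 |
| 0.8 | 0.25 | 0 | 0.85 | 0.80 | 1.06 |
| 0.6 | 0.50 | 0.25 | 0.80 | 0.70 | 1.14 |
| 0.8 | 0.50 | 0.25 | 0.90 | 0.85 | 1.06 |

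Setting c = 0 is the extreme case for controls. The last two rows show how the ratio falls once usual care finds some events.

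**4. Effect on the 10% versus 25% contrast, 160 per group.**

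- s = 0.6, v = 0.5, c = 0: observed 0.10·0.80 = 8% versus 0.25·0.60 = 15%. The ratio is 0.53 against a true 0.40, and power is 50%.
- Same, with c = 0.25: 8% versus 0.25·0.70 = 17.5%. The ratio is 0.46 and power is 72%.
- Calls only, s = 0.6 in both arms: 6% versus 15%. The ratio is 0.40 and power is 75%.

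**5. No true difference (25% in both arms).** With s = 0.6, v = 0.5, c = 0, the observed risks are 20% versus 15%. The chance of a significant excess in TAPER is 22%, against a nominal 2.5% in that direction. With c = 0.25 (20% versus 17.5%) it is 8%.

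**The case against.** **The named harms row is narrower than the hypothesis.** Table 1 lists serious adverse events with beneficial withdrawal, at times that appear to be the calls (T1 is not defined in the footnote). No row tests non-serious events or side effects. A reader might infer that the whole safety comparison is compromised, and the documents do not support that. Serious events are defined by outcomes such as hospitalisation or death, and emergency visits can be checked in records, so both depend little on extra clinic contact. What remains exposed is beneficial withdrawal (in that same row), adverse events in general (in the hypothesis) and side effects (in the sample size claim).

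**The per-drug inquiry is the weaker channel.** It takes place before any taper is finalised, so it mostly records existing side effects, and the article does not say that it feeds the event count. This stands. The monitoring visits are the main mechanism, and their frequency is not given.

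**The size is assumed.** This also stands. Controls have a regular physician and can report events, and the calls may pick up events already seen at visits. Both would lower the ratio.

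**Some event types presuppose stopping a drug.** Withdrawal events and unmasked side effects arise mainly in TAPER and are descriptive by nature. This supports listing them by source. It does not support testing the combined count.

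**The detail may lie elsewhere.** Additional Files 4 and 5 and any SAP are not shown and may separate the sources. But the collection rule is stated in this article, and if source is not recorded at collection a later analysis plan may be unable to recover it.

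**Conclusion.** The concern holds in a limited form. As the article describes it, the comparison of non-serious adverse events, side effects and beneficial withdrawal effects is open to detection bias, probably towards more recorded events in TAPER. For adverse events and side effects this runs against the trial's hypothesis. For beneficial withdrawal effects it runs in favour.

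If controls have no spontaneous or clinician detection, three assumed settings give ratios of 1.13 to 1.33 under equal true rates, and the weakest combination tried gives 1.06. With some detection in controls the ratios are smaller. These figures assume that the calls work equally well in both arms and that the other channels act independently of them.

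A reader might go further and say that the comparison is distorted, or that TAPER will look harmful. The documents give no detection rates, so neither can be established. Unblinded patients may also report differently for reasons that have nothing to do with clinic contact.

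**What to change.** 1. Record the source of every event: scheduled call, spontaneous patient report, clinician report, TaperMD record or chart.
2. Base the between-arm comparison of non-serious events, side effects and beneficial withdrawal effects on the 1-week, 3-month and 6-month calls, made with the same questions in both arms.
3. Compare serious adverse events and emergency visits using the same chart and call sources in both arms.
4. List spontaneous, clinician and TaperMD-derived events by arm and source, without a between-arm test.
5. Align the Table 1 hypothesis, its harms row and the side-effect claim under Sample size, so that each names the outcome and source to be compared.

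The cost is one field on the event form and a few lines of analysis text. The tested comparison will contain fewer events, although in the assumed case above it had more power (75% versus 50%) because the contrast was no longer diluted. Every event is still reported and acted on. The change reduces the bias without removing it: patients know their allocation, and those being monitored may also answer the calls differently.

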### Check-in data collection

To facilitate accurate recall of adverse events, healthcare utilization, and changes in symptoms or side effects throughout the study duration, telephone check-ins will occur at 1 week, 3 months, and 6 months post-baseline to enquire specifically about these items. Details of any adverse effects identified at these data collection points will be provided in real time to the family physician and pharmacist to address as clinically appropriate. The research ethics board will be notified of any adverse events felt to be study related.

### Patient and provider experience of TAPER

Patients in the intervention arm of the study will be invited to participate in semi-structured interviews to explore the meaning of current medication practices in the context of their everyday lives and their experience of the deprescribing process. Those who respond and consent to this portion will participate in the qualitative study. Attention will be paid to the biopsychosocial experiences of patients in relation to their experiences of the intervention. We will conduct in-depth interviews at the initial stages of the intervention as well as at the end to get a full picture of their experience with the intervention and process of describing.

In addition, this subset of consenting patients will be asked to keep a diary on their chronic disease management practices, and their experience going through the intervention during the study. The aim is to understand both the experience of the intervention and any effects on the complex work of managing multiple chronic diseases. Research on patient compliance suggest that electronic diaries are effective and reliable sources of data [64]. Patients will also be asked about their satisfaction with the intervention process and with their care around medications using Likert type scales, as well as free text responses of the strengths and weaknesses of the process and whether or not they would recommend the intervention to a family member or friend.

Participating pharmacists and family physicians will be asked to record their experiences and feelings about the deprescribing process as field notes during the study. Semi-structured interviews will be conducted at the end of the study at all sites to gain a more in-depth understanding of their experience of the intervention. A single-item question will also be used to measure one’s confidence in their own ability to undertake a process of deprescribing with their patients using a 5-point Likert scale developed for the study, as well as an open-ended question to describe the five best and five worst aspects of the intervention. A validated scale that maps to Normalization Process Theory, the NoMAD survey, is a 23-item survey that will be used to measure implementation processes from the perspectives of those directly involved in implementation of the intervention as the study progresses [65, 66].

### Economic analysis

A 6-month trial-based economic evaluation will be conducted to compare the costs and quality-adjusted life years (QALYs) associated with the intervention and control groups (Research Question 3). Costs will be derived from health care resource utilization data collected in the case report forms and the medical records (e.g., hospitalization, emergency room visits, medication use, home care services, physiotherapy, home care visits). Fixed and variable costs associated with developing and implementing the intervention will be based on trial data. In the base case analyses, Ontario unit costs will be used to cost the healthcare resource utilization and the program costs. To calculate the QALYs, the health utility scores derived from the EQ-5D-5L questionnaire using the Canadian algorithm [67] will be weighted by time spent in health states using an area-under-the-curve approach. Healthcare resource utilization and EQ-5D-5L data will be collected at baseline and at 6 months. Techniques to deal with missing data and censored data will be considered as appropriate [68]. Bootstrap techniques will be used to deal with sampling uncertainty and cost-effectiveness acceptability curves will be used to determine the probability of the intervention to be cost-effective at different willingness-to-pay thresholds ($50,000 or $100,000/QALY gained). The economic evaluation will be conducted according to Canadian [69] and international [68] guidelines and from a Ministry of Health perspective. Because the duration of the study is 6 months, there is no discounting of costs or effects (QALY’s).

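### Baseline utility carries half the weight of the six-month QALY, and the economic analysis states no baseline adjustment; adding one would sharpen the incremental QALY at no cost in data

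*Protocol article*

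**What the plan says.** The Economic analysis section of the protocol article plans a trial-based evaluation over 6 months that compares costs and QALYs between the two arms. Utilities come from the EQ-5D-5L with a Canadian value set and "will be weighted by time spent in health states using an area-under-the-curve approach". On timing it says "Healthcare resource utilization and EQ-5D-5L data will be collected at baseline and at 6 months". On inference it says "Bootstrap techniques will be used to deal with sampling uncertainty and cost-effectiveness acceptability curves will be used", with thresholds of $50,000 and $100,000 per QALY. It adds that "The economic evaluation will be conducted according to Canadian [69] and international [68] guidelines".

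Table 1, under Data management, gives the method for cost per QALY only as "Cost utility analysis", timed at 6 months, with no hypothesis. The regression plan under Quantitative data analysis mentions neither QALYs nor costs. Allocation and randomization says that randomisation is stratified by site. No section names a covariate for the QALY or cost comparison, and none says that there will be none.

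**The concern.** With only two utility measurements, the area under the curve is a plain average of the baseline and 6-month values multiplied by half a year. Half the weight therefore falls on a number that TAPER cannot have changed. If the arms differ by chance at baseline, that difference is counted as QALYs gained or lost, and it carries over into the 6-month value to the extent that the two are correlated. The bootstrap describes the resulting uncertainty but does not reduce it.

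This matters because the signal is small. Any true effect reaches the incremental QALY as only a quarter of the 6-month utility difference. The baseline values that would remove the noise are already being collected.

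**Working it through.** The article gives no utility SD, correlation or QALY precision, so there is no figure of the plan's own to reproduce.

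**Inputs from the article:** utilities at 0 and 6 months and a horizon of 0.5 years (Economic analysis); 1:1 allocation (Research design); n = 160 per arm after attrition (Sample size).

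**Assumed, because the article gives no value:** utility SD σ = 0.20 (range 0.15 to 0.25), equal at both times unless stated; correlation ρ between u0 and u6 of 0.3, 0.5 or 0.7.

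**1. Weight of baseline.** QALY = 0.5 × (u0 + u6)/2 = 0.25u0 + 0.25u6.

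**2. Variance of the difference between arms.**
- Raw: (2/n) × 0.0625 × σ² × 2(1 + ρ)
- Adjusted for u0: (2/n) × 0.0625 × σ² × (1 − ρ²)
- Ratio, adjusted to raw: (1 − ρ)/2

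| ρ | variance left | variance cut | SE ratio |
|---|---|---|---|
| 0.3 | 35% | 65% | 0.59 |
| 0.5 | 25% | 75% | 0.50 |
| 0.7 | 15% | 85% | 0.39 |

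At ρ = 0 the cut is still 50%. The ratio does not depend on σ or n. If the SD at 6 months is k times that at baseline, the ratio becomes k²(1 − ρ²)/(1 + k² + 2ρk). For k of 0.8 to 1.25 and ρ of 0.3 to 0.7, the cut is 57% to 88%.

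**3. Scale at ρ = 0.5 and σ = 0.20.**
- Raw SE = √(0.0125 × 0.0625 × 0.04 × 3) = 0.0097 QALY.
- Adjusted SE = √(0.0125 × 0.0625 × 0.04 × 0.75) = 0.0048 QALY.
- At σ = 0.15 the pair is 0.0073 and 0.0036; at σ = 0.25 it is 0.0121 and 0.0061.
- A simulation of 4,000 trials at ρ = 0.6 and σ = 0.20 gave 0.0101 and 0.0044, against 0.0100 and 0.0045 from the formulas.

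**4. One-SE baseline imbalance.** The SE of the baseline difference is 0.20 × √(2/160) = 0.022. Its direct effect on the QALY difference is 0.25 × 0.0224 = 0.0056. With carry-over to 6 months at ρ = 0.5 it is 0.25 × 1.5 × 0.0224 = 0.0084, or about $420 per patient at $50,000 per QALY.

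**5. Net benefit, with cost noise included.** At $50,000 the QALY part of the 95% half-width is 1.96 × SE × 50,000, which is $949 raw and $474 adjusted. The cost part is 1.96 × cost SD × √(2/160). The article gives no cost SD, so a range is assumed, with zero cost–QALY correlation and costs left unadjusted:

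| cost SD | raw | adjusted | cut |
|---|---|---|---|
| $2,000 | $1,045 | $646 | 38% |
| $5,000 | $1,450 | $1,194 | 18% |
| $10,000 | $2,388 | $2,242 | 6% |

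At $100,000 the QALY part doubles ($1,898 and $949) and the cost part does not change. The same three cost SDs then give cuts of about 46%, 34% and 18%.

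**The case against.** The strongest reply is that the article never says the comparison is unadjusted. The area-under-the-curve sentence defines each patient's QALY, not the model that compares the arms. Both that definition and the bootstrap are compatible with regression on baseline utility, and the fix proposed here keeps both. The section is a summary: it leaves missing-data techniques open and defers to guidelines whose content is not shown. Covariates for an incremental-QALY model are commonly left to an analysis plan or health-economic plan. All of this stands. A reader might infer that the trial has committed itself to a raw comparison, but the text does not support that.

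Three further inferences also go too far:

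- **Bias.** Randomisation makes even the raw difference unbiased over repeated trials, and the bootstrap would reflect its uncertainty properly. What is lost is precision, together with error conditional on the imbalance actually observed.
- **An acceptability curve dominated by pre-treatment differences.** The curve also carries cost variance. Step 5 shows that the gain could be large or slight.
- **Low power for QALYs.** The SEs could be turned into power, but Table 1 sets no hypothesis for cost-effectiveness and no test of QALYs is planned.

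What survives is narrower. The comparison actually described has an estimator available that is clearly better, and nothing in the article says that it will be used.

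**Conclusion.** The point holds as a low-cost improvement, not as an error in the plan. The half weight of baseline utility follows from the article's own two-point design and needs no assumption. With equal SDs, adjustment removes more than half of the variance of the QALY difference at any positive correlation. On the SE scale it removes more than half only when the correlation exceeds 0.5, so to say that most of the precision is lost would be safe for the variance but not for the SE.

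The absolute figures (SE, dollars per patient, net-benefit half-widths) rest on assumed SDs and correlations and show scale only. Whether the trial would in fact run the raw comparison cannot be settled from this article.

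**What to change.** Add to the Economic analysis section, or confirm if a fuller economic plan already says so:

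- Incremental QALYs are estimated by regression of the QALY on arm, baseline EQ-5D-5L utility and site (the randomisation stratum).
- Incremental costs are estimated by regression on arm, site and baseline resource-use cost, where that is available.
- Patients are resampled with their cost and QALY kept together, and both models are refitted in each bootstrap sample. The ICER and acceptability curves are built from the adjusted differences.

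This takes a sentence or two. Baseline EQ-5D-5L and resource use are already scheduled, so there is no added burden on patients, and randomisation keeps the adjusted comparison valid. Fixing the model before the arms are unblinded also removes a later choice between a raw and an adjusted estimate that might fall on opposite sides of a threshold.
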